This study aims to evaluate the efficacy and safety of Qizhi Jieyu pill in the treatment of patients during the recovery phase of cerebral infarction through a randomized controlled clinical trial. We hypothesize that the addition of Qizhi Jieyu pill to conventional treatment will result in greater improvement in National Institutes of Health Stroke Scale (NIHSS) scores and lower recurrence rates compared to conventional treatment alone.

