#### Conditions and Procedures for Participant Withdrawal

There are two routes for participant withdrawal.

Withdrawal determined by the investigator: This may occur when a participant already enrolled in the study becomes unsuitable for continued participation due to the development of complications, comorbidities, or special physiological changes. Other conditions include poor compliance, defined as taking less than 80% or more than 120% of the prescribed medication, and the use of prohibited medications as per protocol.

Participant-initiated withdrawal: According to the informed consent form, participants have the right to withdraw at any time. If a participant stops taking the medication or attending visits without formally withdrawing, they are still considered “withdrawn” (or “lost to follow-up”). Reasons for withdrawal should be documented where possible and may include feeling the treatment is ineffective, the development of intolerable adverse reactions, personal circumstances, financial reasons, or unexplained loss to follow-up.

Regardless of the reason, case report forms for withdrawn participants should be retained. The last recorded test results will be used as final data, and both efficacy and adverse events will be analyzed in the full dataset.

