#### Secondary Outcomes

The 3 secondary outcomes are the change in TCM syndrome scores, cerebral infarction recurrence rates, and the change in Rankin Scale scores.

A comparison of TCM syndrome scores before and after the medication will be conducted. Based on the guiding principles for clinical research of new Chinese medicines [22], efficacy is categorized as cured, markedly effective, effective, or ineffective according to the change in TCM syndrome scores. TCM symptoms include dizziness, headache, irritability, limb stiffness, neck stiffness, limb numbness, excessive phlegm, shortness of breath, fatigue, spontaneous sweating, dry stool or constipation, dry mouth or thirst, red or dark tongue, and yellow-greasy tongue coating.

In addition, we will use an intelligent TCM diagnostic device (produced by Shenzhen Huiyibida Medical Technology Co, Ltd) to collect tongue images, tongue coating, and pulse information from patients at multiple timepoints. Two study physicians will independently record patients’ clinical symptom information to monitor changes in TCM symptoms and the potential evolution of syndromes.

The cerebral infarction recurrence rate will be evaluated every 12 weeks by CT or MRI and calculated as the number of recurrent cases / the total study population × 100%.

Finally, a comparison of pretreatment and post-treatment Rankin Scale scores will be conducted [23]. The Rankin Scale evaluates neurological recovery after stroke in 6 levels: 0=no symptoms at all, 1=symptoms present but no significant disability, 2=slight disability, 3=moderate disability, 4=moderately severe disability, 5=severe disability, and 6=death.

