### Statistical Analysis

#### Definition and Selection of Statistical Analysis Datasets

Participants will be categorized into the following analysis sets:

Full analysis set: This includes all randomized participants who have at least 1 postbaseline efficacy evaluation. This is the main dataset for efficacy analysis. Missing values for primary efficacy outcomes will be imputed using the last observation carried forward method. Missing values for secondary efficacy and safety outcomes will not be imputed. For secondary efficacy endpoints and safety data, descriptive analysis and complete-case analysis will be conducted based on actual observed values. Although last observation carried forward is commonly used in clinical trials, we acknowledge its limitations in progressive conditions such as stroke recovery. We will perform sensitivity analyses using multiple imputation methods to evaluate the robustness of our results.Per protocol set: This includes all participants in the full analysis set who meet inclusion criteria, do not meet exclusion criteria, complete the treatment, and do not have major protocol deviations. This is the secondary dataset for efficacy evaluation.Safety set: This includes all randomized participants who received at least 1 dose of Qizhi Jieyu pill and had at least 1 postbaseline safety evaluation.

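### The recurrence rate has no single agreed denominator: three stated rules treat participants lost without a recorded recurrence differently

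*Protocol article*

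**What the plan says.** Four places in the protocol article bear on this outcome.

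- **Introduction (hypothesis).** Besides greater NIHSS improvement, the trial expects "lower recurrence rates compared to conventional treatment alone".
- **Secondary Outcomes.** "The cerebral infarction recurrence rate will be evaluated every 12 weeks by CT or MRI", and the rate is "calculated as the number of recurrent cases / the total study population × 100" (per cent). The formula has no term for length of follow-up and no rule for participants who were not scanned.
- **Definition and Selection of Statistical Analysis Datasets.** "Missing values for secondary efficacy and safety outcomes will not be imputed"; for secondary endpoints, "descriptive analysis and complete-case analysis will be conducted based on actual observed values". The main efficacy set is the full analysis set: "This includes all randomized participants who have at least 1 postbaseline efficacy evaluation".
- **Conditions and Procedures for Participant Withdrawal.** For those who leave, "The last recorded test results will be used as final data, and both efficacy and adverse events will be analyzed in the full dataset".

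The Sample Size Calculation section plans 63 participants per group with 20% dropout overall, and is based on NIHSS change only. The Statistical Analysis Plan section names chi-square or Fisher tests for categorical variables. No expected recurrence rate appears anywhere.

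**The concern.** Take a participant scanned without recurrence at week 12 and then lost. Under the Secondary Outcomes formula this person is in the denominator and counts as a non-case for all 48 weeks. Under the complete-case rule the week-48 status is missing and is not imputed, so the person drops out of the analysis. Under the withdrawal rule the week-12 result becomes the final result. That again makes the person a non-case, and it is a form of carrying forward, which sits badly with the statement that secondary outcomes are not imputed. A participant with no postbaseline evaluation is counted under the first rule and excluded from the full analysis set.

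An analyst could follow any of these rules and claim to comply, and the choice could be made after the data are seen. The formula also credits lost participants with event-free time that nobody observed. That lowers the estimated risk, and lowers it more in the arm with more dropout. Participants and clinicians are not blinded, so unequal dropout is possible.

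**Working it through.** **There is no plan figure to reproduce.** The protocol gives no recurrence risk, no dropout by arm and no dropout timing. The inputs taken from the document are 63 per arm, 20% dropout, and scans at weeks 12, 24, 36 and 48. The assumptions are a true 48-week risk R = 10% (range 5% to 20% below), constant hazard, and dropout independent of recurrence.

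**1. One set of counts under different rules.** With 20% dropout, 63 × 0.8 = 50.4, so about 50 per arm reach week 48. Suppose six recurrences are recorded in an arm:

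- all randomised: 6/63 = 9.5%
- week-48 completers, if all six are among them: 6/50 = 12.0%
- full analysis set, if three participants have no postbaseline evaluation: 6/60 = 10.0%

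**2. Continuous detection, dropout uniform over 48 weeks.** The observed proportion over all randomised is (1 − d)R + d·m, where m is the mean risk accrued by the time of dropout. With λ = −ln(0.9) = 0.1054, m = 1 − 0.1/0.1054 = 0.051. At d = 0.2: 0.8 × 0.10 + 0.2 × 0.051 = 0.090, so **9.0%** against a true 10%.

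**3. Detection only at the 12-weekly scans.** The risk per interval is q = 1 − 0.9^(1/4) = 0.0260. Cumulative risk at the four visits is 0.0260, 0.0513, 0.0760 and 0.1000. With even dropout, 5% are lost before each visit:

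- all randomised: 0.05 × (0 + 0.0260 + 0.0513 + 0.0760) + 0.80 × 0.10 = 0.0877
- full analysis set: 0.0877/0.95 = 0.0923
- known status (recorded recurrence, or scanned at week 48): 0.0877/(0.0877 + 0.80 × 0.90) = 0.109

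If all dropout comes before week 12: all randomised 0.80 × 0.10 = 0.080; full analysis set 0.080/0.80 = 0.100; known status 0.080/(0.080 + 0.720) = 0.100.

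| Denominator (true risk 10%) | Even dropout | All before week 12 |
|---|---|---|
| All randomised | 8.8% | 8.0% |
| Full analysis set | 9.2% | 10.0% |
| Known status | 10.9% | 10.0% |
| Week-48 completers | 10.0% | 10.0% |

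For other true risks, cases over all randomised give 4.0–4.4% (true 5%), 12.0–13.2% (true 15%) and 16.0–17.6% (true 20%). The relative understatement is about 12% to 20% throughout.

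**4. Unequal dropout with the same true risk of 10% in both arms, cases over all randomised.**

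- 10% versus 30% dropout, continuous detection: 9.5% versus 8.5%, a gap of about 1.0 point.
- 10% versus 30%, 12-weekly detection: 9.38% versus 8.15% with even dropout (gap 1.2 points, ratio 0.87), or 9.0% versus 7.0% with early dropout (gap 2.0 points, ratio 0.78).
- 15% versus 25%, 12-weekly detection: gap 0.6 to 1.0 point, ratio 0.93 to 0.88.

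**5. Scale of that gap.** The standard error of the difference at 10% risk is √(2 × 0.10 × 0.90/63) = 0.053, or 5.3 points. A gap of 1.0 to 2.0 points is about 0.2 to 0.4 standard errors.

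**The case against.** The strongest reply is that a fixed 48-week proportion is a legitimate secondary outcome. The choice of estimator and the censoring rule commonly belong in the statistical analysis plan, which is said to exist and is not shown. That stands: the lack of a named time-to-event method is not in itself a fault. It does not remove the conflict, because all three rules are written in this article.

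The reply can add that the bias is small. At 10% risk and 20% dropout, 9.0% instead of 10% is about 0.6 of a participant among 63. The false gap between arms needs an assumed dropout imbalance, since the protocol gives only an overall 20%, and it is well inside one standard error. This also stands, and it limits the severity.

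Three stronger readings are tempting, and the document does not support them:

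- A reader might infer that the total study population means both arms together, so that each arm's rate would be halved. A consistent pooled reading pools the cases too: six per arm gives 12/126 = 9.5%, the same as 6/63. The planned between-group tests need arm-level denominators in any case. The wording is loose, but it is no plan to divide one arm's cases by 126.
- A reader might infer that everyone lost is counted as recurrence-free. A participant whose recurrence was recorded before leaving still counts as a case. Only those lost without a recorded recurrence are affected.
- A reader might infer that the complete-case rule deletes recurrences recorded before withdrawal. That is one possible reading. The same sentence refers to values actually observed, and the withdrawal section keeps the last recorded result, so the opposite reading is at least as natural. No figure here depends on it.

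**Conclusion.** The point holds as a conflict within the document. The Secondary Outcomes formula, the complete-case rule and the last-result rule do not fix one denominator for participants without a week-48 recurrence assessment, and recurrence is named in the hypothesis. This conclusion needs no assumption about recurrence risk.

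The size does rest on assumptions. With a true risk of 10%, 20% dropout and dropout independent of recurrence, cases over all randomised give about 9.0%, or 8.0% to 8.8% under 12-weekly detection. If the total study population is taken to be the full analysis set, the figure is 9.2% to 10.0%. Unequal dropout would bias the comparison modestly towards the arm that loses more participants. The document does not say which arm that would be, and the material does not show that the choice of denominator would reverse a conclusion about treatment.

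The severity is minor: one of three secondary outcomes is affected, and the primary analysis is untouched.

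**What to change.** Reconcile the Secondary Outcomes, analysis-set and withdrawal sections so that one rule governs recurrence, and exempt recurrence from both the complete-case rule and the last-result rule. Then define the outcome as follows:

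- the 48-week cumulative incidence of first recurrence, per randomised arm, in all randomised participants
- every recurrence observed before withdrawal is kept
- participants without recurrence are censored at their last recurrence assessment; last contact would credit unscanned time as event-free
- a Kaplan-Meier-type or interval-censored estimator, the latter suiting 12-weekly imaging, with death handled as a competing event
- the between-arm difference with its 95% CI

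State also that recurrence is not a powered hypothesis, since the sample size rests on NIHSS change alone.

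The cost is protocol and analysis-plan wording plus slightly more analysis work. The scheduled scans already supply the assessments; the analysis also needs each scan's date, which the visit schedule implies but does not state. The reported uncertainty will be somewhat wider.

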#### Safety Outcomes

Safety will be assessed using the following monitoring indicators:

Vital signs, including temperature, blood pressure, respiration rate, and heart rate, checked every 12 weeks.Routine tests, including blood, urine, and stool tests, every 12 weeks.Other labs and diagnostics, including electrocardiograms, liver function tests (alanine aminotransferase, aspartate aminotransferase, gamma-glutamyltransferase, alkaline phosphatase, and total bilirubin), and kidney function tests (blood urea nitrogen and creatine), every 12 weeks.Adverse events: From the time the participant enters the study until the final follow-up, adverse events will be monitored for 48 weeks. All information related to adverse events will be carefully recorded at all times. Serious adverse events refer to any unexpected clinical events occurring at any dose that result in hospitalization, prolongation of existing hospitalization, disability, impaired ability to work, life-threatening conditions or death, or congenital malformations. Serious adverse events will be reported to the study center and the principal medical ethics committee. In addition, they will be reported to the National Medical Products Administration within 24 hours. Meanwhile, we will specifically record adverse events potentially related to animal-derived components, such as itching, rash, allergic reactions, and gastrointestinal discomfort.

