### Intervention

Referring to the guidelines for clinical management of cerebrovascular diseases in China (second edition) [20], both groups will receive conventional rehabilitation training guidance, including assessment and rehabilitation of cognitive function, speech ability, swallowing function, limb motor and sensory function, balance, psychological state, and daily living abilities. They will also receive standard treatments such as antiplatelet therapy, lipid-lowering and blood pressure control, plaque stabilization, and electrolyte balance maintenance.

On the basis of conventional treatment, the study group will take Qizhi Jieyu pills, 9 g per dose, twice daily after meals. The control group will receive conventional treatment only. The intervention period is 12 weeks, with a total follow-up period of 48 weeks.

All TCM drugs with the same therapeutic effect as the investigational drug (including those with similar indications or efficacy stated in the instructions) are prohibited during the study. All concomitant medications and treatments (ie, for other diseases) must be recorded in the concomitant medication log.

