### Randomization

Random numbers will be generated using SAS statistical software (version 9.4), and participants will be assigned to the intervention and control groups in a 1:1 ratio. After screening and informed consent, patients will be randomly assigned to one of the two groups based on their order of enrolment. The drug number for each participant will remain unchanged throughout the study. In the case of a clinical emergency, the participant’s random code and group assignment may be unblinded.

Due to the nature of the intervention, participant and clinician blinding is not feasible. However, outcome assessors will be blinded to group assignments to minimize detection bias, especially for subjective measures such as TCM symptom scores.

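### The serious adverse event definition requires the event to be unexpected, so foreseeable serious events can miss the label and its expedited reporting

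*Protocol article*

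**What the plan says.** The adverse event bullet under Safety Outcomes in the protocol article contains the only definition of a serious adverse event in the document: "Serious adverse events refer to any unexpected clinical events occurring at any dose that result in hospitalization". The list of consequences continues with prolonged hospital stay, disability, reduced capacity to work, danger to life, death and congenital malformation.

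Serious status has consequences. Such events go to the study center and the ethics committee, and "they will be reported to the National Medical Products Administration within 24 hours".

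Around that sentence, the bullet is broad. On duration it says: "From the time the participant enters the study until the final follow-up, adverse events will be monitored for 48 weeks". On extent it says: "All information related to adverse events will be carefully recorded at all times". Neither statement depends on treatment arm, dosing or expectedness. The bullet closes by naming in advance some reactions to be recorded specifically because of the pill's animal-derived ingredients; allergic reactions are among them.

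Three other places bear on the point:

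- Secondary Outcomes makes recurrent infarction an outcome: "The cerebral infarction recurrence rate will be evaluated every 12 weeks by CT or MRI".
- Intervention gives the control arm neither the pill nor a placebo: "The control group will receive conventional treatment only".
- Definition and Selection of Statistical Analysis Datasets describes the safety set: "This includes all randomized participants who received at least 1 dose of Qizhi Jieyu pill and had at least 1 postbaseline safety evaluation".

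**The concern.** Seriousness describes what an event led to. Expectedness describes whether it was foreseen. An event can be both serious and expected, and in a population recovering from stroke many of the worst events will be. The definition as written admits only events that are serious and also unexpected.

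Two things are at stake. First, a foreseeable event with a grave consequence can be left without the serious label, and so without the ethics committee and regulator reports that depend on it. Second, whether something was unexpected is a judgement. The Randomization section says that participants and clinicians cannot be blinded, so the same event could be classified differently by arm. Safety is half of the trial's stated aim, and the definition should not turn on such a judgement.

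**Working it through.** No arithmetic underlies the definition, and the plan gives no figure to reproduce. The check is to set the passages side by side and apply the sentence to cases that the protocol itself foresees.

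**Step 1: conditions in the sentence.** As written, two conditions must both hold: (a) the event is unexpected, and (b) it led to one of the listed consequences. Removing (a) leaves seriousness resting on (b) alone.

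**Step 2: which events the protocol foresees.** Recurrent infarction is scanned for every 12 weeks, the Introduction describes recurrence under current treatment as high, and the hypothesis concerns lowering it. Allergic and gastrointestinal reactions are named beforehand in the safety bullet. The article does not define expected, so treating these events as expected is a natural reading but not a stated rule.

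**Step 3: apply both versions.**

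| Event | Condition (b) met? | Foreseen in the protocol? | Serious as written, read literally | Serious by consequence alone | Recorded in any case? |
|---|---|---|---|---|---|
| Hospitalisation or death from recurrent infarction | Yes | Yes, as a secondary outcome | Can be left out | Yes | Yes, as adverse event and as recurrence |
| Hospitalised allergic reaction to the pill | Yes | Yes, named in the safety bullet | Can be left out | Yes | Yes, as adverse event |
| Hospitalisation for something nobody foresaw | Yes | No | Yes | Yes | Yes, as adverse event |
| Mild rash, no listed consequence | No | Yes | No | No | Yes, as adverse event |

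The two versions differ only in the first two rows. Those rows hold the severe events that the protocol itself leads one to anticipate: one from the disease, one from the product.

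**Step 4: what is lost.** The last column is yes throughout, because all adverse event information is to be recorded for every participant from entry. The loss is confined to the serious label, any count built on that label, and the reports that follow from it.

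**Step 5: the control arm.** The planned size is 126, and "participants will be assigned to the intervention and control groups in a 1:1 ratio", so 126 / 2 = 63 are controls. None of them takes the pill by design. The safety set requires at least one dose of it, so at most 126 − 63 = 63 participants can enter the set, and 63 / 126 = 50% of those randomized are outside it. A serious event in a control participant would be recorded, but no control participant belongs to the set defined for safety analysis.

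**The case against.** The strongest reply is that this is a slip of wording. *Untoward* fits the sentence where *unexpected* stands, and an investigator may well report a fatal recurrence whatever the adjective. The document is also a journal article, and the full protocol or the case report form guide may have the right word. Both points are fair, and neither can be confirmed from what is shown. The article states the rule positively and offers no second definition, so this is wording stated wrongly and not detail left to another document. Two sites working from paper forms could apply it differently.

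A second reply is that the events are not lost. This stands: the recording rule is unconditional, recurrence is counted separately, and death is a level of the Rankin Scale. The consequence must be limited accordingly.

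A reader might also infer three stronger things that the documents do not support:

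- *That the phrase about dose shuts control participants out of the definition.* The phrase most naturally means whatever the dose. The same bullet monitors every participant from entry, and Table 1 marks adverse events at all four follow-up visits without separating the arms. The explicit exclusion of controls is in the safety set.
- *That a number of missed events can be given.* The article states no recurrence risk, and recurrence found on a scheduled scan need not involve hospitalisation. Any count would stack an assumed risk on the further assumptions that every recurrence is hospitalised and every one is withheld as expected.
- *That a comparison of serious events between arms would be worthless.* The Statistical Analysis Plan section describes no such comparison. Its only statement specific to adverse events concerns those linked to animal-derived ingredients.

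**Conclusion.** The point holds in a limited form. The definition wrongly makes expectedness part of seriousness. Read literally, it allows foreseeable serious events to miss the serious label, the ethics committee report and the 24-hour report to the regulator. It does not remove them from the trial's data.

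The number of events affected cannot be derived from the document, and the defect does not depend on it. A difference in classification between arms is possible because treating staff are unblinded. It assumes that unblinded staff judge expectedness, and the article does not say who does.

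The conclusion rests on a literal reading of the sentence and on treating recurrence and the named reactions as expected. A lenient reader could avoid the problem in practice, but a reporting rule should not depend on that. The correction is worth making because it costs almost nothing and bears on participant safety. The safety set's exclusion of 63 of 126 participants is a separate sentence with a related effect: correcting the definition alone would leave it in place.

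**What to change.** 1. In Safety Outcomes, replace *unexpected* with *untoward* and define a serious adverse event by the listed consequences alone. Suggested wording: any untoward clinical event in a participant of either arm, whether or not expected and whether or not related to study treatment, that results in one of the listed consequences.
2. Assess expectedness separately, so that it describes a serious event and does not decide whether the event is serious.
3. Reconcile the safety set with this definition so that control participants, who receive no pill by design, are covered.
4. Check the full protocol and the case report form guide for the same wording. If either already has the correct definition, bring the article into line with it and record the correction in the registry, where the article says amendments will be recorded.

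The cost is one sentence in the definition, one in the safety set and a line in the form guide. Sites will report slightly more events. Sample size, visits and the primary analysis are unaffected.

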### Study Procedures

Table 1 outlines the specific measurements and timepoints for data collection in this study. Eligible participants will undergo a 1-week preintervention screening period, a 12-week treatment period, and a total 48-week follow-up period. After the study begins, all enrolled participants will have follow-up visits every 12 weeks. All participants will be informed of the study through oral and written information and will be required to sign an informed consent form.

**Table 1 table1:** Clinical trial research timeline.

Item		Screening period and baseline	Visit 1	Visit 2	Visit 3	Visit 4
Visit time		–7 to 0 days	12 weeks ± 7 days	24 weeks ± 7 days	36 weeks ± 7 days	48 weeks ± 7 days

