#### Statistical Analysis Plan

A statistical analysis plan was formulated prior to the start of the study. It will be finalized after discussion among the statisticians, principal investigators, and sponsor before database lock. This plan describes only the standard statistical requirements.

Statistical analysis will be conducted using SAS version 9.4. All hypothesis tests will be 2-sided, with a significance level of α=.05. *P* values less than or equal to .05 will be considered statistically significant.

For continuous variables, mean, SD, minimum, maximum, and median values will be used for descriptive statistics. Independent samples *t* tests (for normally distributed data) or Wilcoxon rank-sum tests (for non-normally distributed data) will be used for hypothesis testing. Normality of continuous variables will be assessed using the Shapiro-Wilk test before choosing appropriate parametric or nonparametric tests.

For categorical variables, frequency and percentages will be used for description. Chi-square tests or Fisher exact tests will be used for hypothesis testing. Ordinal variables will be analyzed using the Wilcoxon rank-sum test.

Logistic regression will be used to control for confounding factors affecting the outcome measures. We will also analyze the association between syndrome evolution patterns and therapeutic efficacy. In parallel, multivariate linear regression will be used to explore the relationship between outcomes and potential confounders, such as baseline NIHSS score, study center, age, and sex. For adverse events potentially associated with animal-derived components—including itching, rash, allergic reactions, and gastrointestinal discomfort—we will conduct attribution analysis and report their incidence separately.

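### Special recording and separate incidence of itching, rash, allergic and gastrointestinal events are tied to suspected relation to the pill, so as worded the reported incidence has no concurrent control rate

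*Protocol article*

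**What the plan says.** The Safety Outcomes section of the protocol article first sets a general rule: "From the time the participant enters the study until the final follow-up, adverse events will be monitored for 48 weeks", and "All information related to adverse events will be carefully recorded at all times". It then adds a targeted rule: "we will specifically record adverse events potentially related to animal-derived components, such as itching, rash, allergic reactions, and gastrointestinal discomfort".

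The Statistical Analysis Plan section takes up the same class, again worded as events potentially associated with animal-derived components, and states that "we will conduct attribution analysis and report their incidence separately". No between-arm comparison is mentioned for it.

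Three other places bear on who can enter that class and who judges entry:

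- Intervention: "The control group will receive conventional treatment only". There is no placebo.
- Definition and Selection of Statistical Analysis Datasets, on the safety set: "This includes all randomized participants who received at least 1 dose of Qizhi Jieyu pill and had at least 1 postbaseline safety evaluation".
- Randomization: "participant and clinician blinding is not feasible". Outcome assessors are to be blinded, with subjective measures such as TCM symptom scores singled out. Nothing says that this extends to judging the cause of adverse events.

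**The concern.** The four named symptoms are non-specific. Both arms receive several conventional treatments, and the article's own TCM symptom list (Secondary Outcomes) includes dry stool or constipation, so bowel complaints are expected in this population with or without the pill. A crude incidence in the pill arm therefore says little about the pill. What is informative is the excess over a concurrent control rate, which a randomised trial is well placed to supply.

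The targeted rule instead selects events by suspected relation to a product that only one arm receives. The unblinded setting can then distort the figure in either direction. Staff may note or attribute more symptoms because the patient takes a pill with animal-derived components, or they may set pill-arm events aside as unrelated. Without an all-cause rate in controls, neither can be checked. Evaluating safety is a stated objective of the trial, and these are the reactions that the article itself chose to single out.

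**Working it through.** The article gives no adverse-event rate, so there is no figure to reproduce. The check is mainly a comparison of the rules.

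**Step 1: who can enter each record or analysis?**

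| Rule | Section | Condition for entry | Open to controls? |
|---|---|---|---|
| General recording | Safety Outcomes | Any adverse event, study entry to week 48 | Yes |
| Visits | Study Procedures: "all enrolled participants will have follow-up visits every 12 weeks" | Enrolment | Yes |
| Adverse events at visits 1 to 4; diary cards | Table 1 | No split by arm | Yes |
| Special recording | Safety Outcomes | Possible relation to the pill's animal components | Not on a literal reading |
| Attribution analysis and separate incidence | Statistical Analysis Plan | Same | Not on a literal reading |
| Safety set | Analysis datasets | At least one dose of the pill | No, if treated as assigned |

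A rash in a control should therefore exist in the data as an ordinary adverse event. It does not qualify for the targeted class as worded, and its owner is not in the safety set.

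**Step 2: denominator.** Sample Size Calculation plans 63 per group, 126 in total. The safety set can hold at most 63 of 126 (50%), with 0 of 63 controls if all are treated as assigned.

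**Step 3: what would unequal recording do?** This is an illustration only, because every rate is assumed. Let p be the true incidence, equal in both arms and fully recorded with the pill. Let f be the fraction of control events recorded for the same terms. The spurious difference is p − f × p = p(1 − f).

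| p (assumed) | f = 1 | f = 0.75 | f = 0.5 | f = 0 |
|---|---|---|---|---|
| 5% | 0 | 1.25 points | 2.5 points | 5 points |
| 10% | 0 | 2.5 points | 5 points | 10 points |
| 20% | 0 | 5 points | 10 points | 20 points |

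At p = 10% the expected pill-arm count is 63 × 0.10 = 6.3. In controls it is 63 × 0.10 × 0.75 = 4.7, 63 × 0.10 × 0.5 = 3.2, or 0.

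The f = 0 column is what the literal class definition yields if its control count of zero is set beside the pill arm: the whole background rate looks like a pill effect. The f = 1 column is equally compatible with the article if recording is in practice the same in both arms. If pill-arm events are dismissed as unrelated, the error runs the other way. The document does not allow a choice among these cases.

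**The case against.** A reader might infer more: that controls' itching, rash or bowel symptoms will go unrecorded, or that the pill arm will be prompted and controls will not, so that ascertainment is known to differ. The article does not support this. Recording at all times, 48 weeks of monitoring, 12-weekly visits and diary cards carry no restriction by arm. Prompting, checklists and solicitation are never mentioned, and specific recording may mean no more than flagging events of interest. Any risk ratio built on assumed prompted and unprompted capture rates is therefore hypothetical, and no direction of bias is established. It would also go too far to say that the trial cannot estimate the excess risk. If controls were in the safety set, incidence by event term and arm could be tabulated from the general records.

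The wording can also be read more kindly. The four symptoms are introduced as examples, the study group is not named as the only source, and the sentence could be a loosely phrased list of events of special interest for everyone. How events are elicited is, moreover, commonly left to the full protocol or the case report form.

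Most of this stands, and it limits the point to what the text fixes. It does not remove the point. The class is defined by attribution in two separate sections, nothing says that it will be recorded or tabulated in controls, and the safety set leans towards the narrower reading by excluding them. That is a stated rule that works badly, not a detail left out of a condensed article.

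**Conclusion.** The point holds in this form: as worded, the specially recorded and separately reported class is one that untreated controls cannot enter, and the safety set excludes them as well, so the incidence of these symptoms would be reported without a concurrent comparator. This rests on the literal reading of the two sentences and on controls being treated as assigned. The safety-set exclusion does not depend on how those two sentences are read.

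Unequal ascertainment is a risk that follows from attribution-conditioned recording by staff who know the allocation. It is not a stated feature of the plan, and its size cannot be derived from the article; the differences of 0 to 20 points above show only how the assumptions drive the result.

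The consequence is confined to a safety description. It is worth correcting because safety is a stated aim and the change is cheap.

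**What to change.** 1. In Safety Outcomes and in the Statistical Analysis Plan section, define the class by event term (itching, rash, allergic reaction, gastrointestinal discomfort) regardless of suspected cause.
2. State that these terms are recorded in the same way in both arms at the existing visits at weeks 12, 24, 36 and 48.
3. Define the safety set so that it includes controls. This has to accompany item 1: redefining the class alone would still leave controls outside the analysis, while changing the safety set alone would leave the class tied to attribution.
4. Make all-cause incidence by arm, with the risk difference and its 95% CI, the main result for these terms. Keep attribution to animal-derived components as a descriptive supplement for the pill arm.

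The cost is wording in three places, one entry on the existing case report form, and slightly more event recording in controls. No visit is added and no treatment changes. Timing matters: screening began on April 10, 2025, and for visits already held only what was recorded under the general rule can be recovered. The change also does no harm under the kinder reading, since it then only makes that reading explicit.
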